#### Interim Analyses

Interim analyses will be conducted at predetermined intervals to assess the study’s safety, efficacy, and futility. The analyses will be planned to coincide with critical milestones, such as the completion of a specific percentage of follow-up assessments or the occurrence of a predefined number of events. An independent data monitoring committee will be established to oversee interim analyses. The data monitoring committee will consist of experts in the field, statisticians, and clinicians who are not directly involved in the day-to-day conduct of the study. The data monitoring committee will have exclusive access to interim results. Unblinded provisional data will be shared with the data monitoring committee for their assessment of safety, efficacy, and overall study progress.

Clear stopping guidelines will be established in advance, outlining the criteria for stopping the trial. Controlling guidelines will include considerations for both safety and efficacy, with predefined thresholds for statistical significance. The trial may be stopped for the following reasons:

Efficacy: If interim analyses demonstrate overwhelming evidence of benefit, meeting predetermined criteria for early success.Safety: If there is a significant safety concern, meeting predefined criteria for harm.Futility: If interim analyses indicate that the study is unlikely to achieve its primary objectives.

The principal investigator and the steering committee will take the final decision to terminate the trial. The steering committee, comprising key study investigators, will consider the data monitoring committee’s recommendations and ultimately take a decision.

A clear communication plan will be in place to ensure timely and transparent reporting of interim results to relevant stakeholders. Communication channels will be predefined to facilitate the efficient dissemination of information. Any decision to stop the trial will be promptly reported to relevant ethical review boards and regulatory authorities. Transparent reporting ensures compliance with ethical standards and regulatory requirements.

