### Additional Consent Provisions for the Collection and Use of Participant Data and Biological Specimens

We will conduct the trial according to the ICH Good Clinical Practice (GCP) guidelines. Accurate and consistent records are essential to a cooperative study.

The clinical and surgical data collected in a standardized endorsed data set can be downloaded locally and used for internal quality analyses or institutional research. The data collection methodology will use a website platform that meets international data privacy protection standards and rules. Notably, data are anonymously reported, independently accessed, and encrypted for other users.

For joining the database, the login of each institution will be provided after downloading and completing an application form from the project homepage and directly sending an email to the study coordinator. Investigators will access the patient medical records and enter the required data into the database. Protected health information will not be reused or disclosed to any other person or entity, except as required by law, for authorized research project oversight.

In compliance with the ICH-GCP guidelines, the investigator or institution will maintain all electronic case report forms, all source documents that support the data collected from each subject, all study documents as specified in ICH-GCP Section 8 (Essential Documents for the Conduct of a Clinical Trial), and all study documents as determined by the applicable regulatory requirements. The investigator or institution will take measures to prevent accidental or premature destruction of these documents. Essential documents must be retained until at least 25 years after the last approval of a marketing application in an ICH region and until there are no pending or contemplated marketing applications in an ICH region or until at least 15 years have elapsed since the formal discontinuation of clinical development of the investigational product. These documents will be retained longer if required by the applicable regulatory requirements or an agreement with the sponsor. The sponsor is responsible for informing the investigator or institution when these documents no longer need to be retained.

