### Sample Size

LUCENT adopts a nonspecific sample size approach, allowing for the inclusion of eligible participants based on the defined criteria. The study aims to enroll a diverse and representative sample of lung cancer patients diagnosed in early and locally advanced stages to capture a comprehensive range of outcomes and experiences. Participants meeting the inclusion criteria will be recruited consecutively from participating institutions to ensure a systematic and unbiased selection process. The study will involve multiple centers across Italy to enhance the diversity and generalizability of the study findings. Data collection will be facilitated through a web-based registry developed for the study, allowing for standardized and centralized data collection from various participating sites.

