### Recruitment

Recruitment involves the following:

Collaboration with health care institutions: Forge partnerships with a network of health care institutions across Italy.Multidisciplinary team engagement: Involve a multidisciplinary team, including thoracic surgeons, oncologists, and research staff, in the recruitment process.Patient advocacy groups: Partner with patient advocacy groups focused on lung cancer. Leverage these groups to disseminate information, support recruitment efforts, and enhance community trust.Continuous communication: Maintain open and continuous communication with potential participants throughout the recruitment period.Address concerns, provide clarifications, and emphasize the value of their contribution to research.Regular site meetings: Conduct regular meetings with site staff to share best practices, address challenges, and reinforce recruitment strategies. Foster a collaborative and motivated research team.

The study aims to achieve adequate participant enrollment by combining these strategies, ensuring a diverse and representative sample to meet the target sample size within the specified recruitment period.

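### The Interim Analyses section allows an early stop for efficacy in a nonrandomized benchmarking registry, where benefit has no matching primary contrast and a stop could cut the cohort and the 2-year follow-up short

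*Protocol article*

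**What the plan says.** The Interim Analyses section of the protocol article plans repeated looks at safety, efficacy and futility under a data monitoring committee. It promises guidelines in advance, "with predefined thresholds for statistical significance", and continues: "The trial may be stopped for the following reasons". The efficacy reason is "Efficacy: If interim analyses demonstrate overwhelming evidence of benefit, meeting predetermined criteria for early success". The futility reason is "Futility: If interim analyses indicate that the study is unlikely to achieve its primary objectives". The final decision lies with the principal investigator and the steering committee. The section does not say whether a stop would end recruitment only or follow-up as well.

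Other sections describe a different kind of study:

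- Trial Design and the allocation section: a nonrandomized observational cohort in which the researchers do not intervene.
- Primary Objectives (Introduction and Results): national benchmarks from risk-adjusted outcomes and process indicators, and evaluation of centres against them.
- Intervention Description: the surgical approach depends on the tumour, the patient's condition and the surgeon's experience.
- Sample Size: "LUCENT adopts a nonspecific sample size approach". Recruitment, however, speaks of enrolling a sample "to meet the target sample size within the specified recruitment period" and gives no number.
- Participant Timeline: recruitment from 1 January 2024 to 31 December 2026, at least 2 years of follow-up, completion in 2028.

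On access, Interim Analyses states "The data monitoring committee will have exclusive access to interim results", then promises timely reporting of interim results to stakeholders.

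**The concern.** An efficacy stop presupposes a defined contrast whose early resolution makes further data unnecessary, and usually a planned amount of information against which early can be measured. The primary objective here is descriptive and comparative benchmarking of centres, so there is no primary treatment effect for overwhelming benefit to refer to. With an open sample size there is no planned information either.

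The only contrast that could produce a benefit is the one between open, minimally invasive and robot-assisted surgery. That comparison is of interest to the study but is not its primary objective, and by the article's own account patients reach each approach for reasons related to prognosis. A small interim P value would not by itself show that one approach is better.

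Stopping would bring no offsetting gain to participants. The study allocates nobody to an approach, and Provisions for Posttrial Care says standard care continues regardless of participation. The effect of a stop would be lost data: fewer patients in the benchmark cohort if it came during recruitment, and truncated survival and recurrence data if follow-up also ended. Follow-up that is not collected on schedule may not be recoverable.

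**Working it through.** The article gives no boundary, look schedule, alpha or sample size, so there is no figure of the plan to reproduce. The check has two parts.

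**1. What an efficacy stop needs, against what the article provides**

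| Needed | Provided |
|---|---|
| A treatment allocated by the study | None (Trial Design; allocation section) |
| A treatment contrast as primary objective | Benchmarks and centre evaluation (Primary Objectives) |
| Planned information or size | Left open in Sample Size; an unnumbered target in Recruitment |
| A contrast that can support a causal reading of benefit | Approach chosen on tumour, patient and surgeon factors (Intervention Description) |

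None of the four is met for the primary objective.

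**2. What a stop could cost**

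Inputs from Participant Timeline: recruitment from 1 January 2024 to 31 December 2026, which is 366 + 365 + 365 = 1,096 days; minimum follow-up 2 years. Assumptions not in the article: uniform accrual, and a stop that ends all data collection. The stop dates are chosen for illustration.

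- Share enrolled at stop date T = recruitment days elapsed by T / 1,096 (at most 1).
- Share of the planned cohort with 2 years of follow-up = recruitment days elapsed by T minus 2 years / 1,096.
- Standard error of a short-term benchmark (such as length of stay), relative to the full cohort = 1 / √(share enrolled).

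| Stop | Share enrolled | Share with 2 years | SE ratio |
|---|---|---|---|
| Mid-2025 | 547/1,096 = 50% | 0% | 1.42 |
| End 2025 | 731/1,096 = 67% | 0% | 1.22 |
| Mid-2026 | 912/1,096 = 83% | 182/1,096 = 17% | 1.10 |
| End 2026 | 100% | 366/1,096 = 33% | 1.00 |
| Mid-2027 | 100% | 547/1,096 = 50% | 1.00 |
| End 2027 | 100% | 731/1,096 = 67% | 1.00 |
| Mid-2028 | 100% | 912/1,096 = 83% | 1.00 |
| End 2028 | 100% | 100% | 1.00 |

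The mid-2025 ratio is 1.42 by day count and √2 = 1.41 for exactly half the cohort. At that date no patient could have more than 1.5 years of follow-up. The last patient, enrolled on 31 December 2026, reaches 2 years on 31 December 2028, so a full stop at any earlier date breaks the stated minimum for some patients.

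**The case against.** Several counter-arguments have force.

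- **The rule is permissive.** The study may be stopped, and two bodies must decide. This stands: the article does not commit the registry to stopping.
- **Surgical approaches are compared.** The comparator section and the additional outcomes say so, and Methods for Additional Analyses foresees adjusted analyses. A reader might infer that nothing is under test; the documents do not support that. What they support is narrower: no treatment is assigned, and no treatment comparison is primary. Adjustment reduces confounding but does not turn a non-primary, non-allocated contrast into a basis for ending the registry.
- **Futility can fit a registry.** Being unlikely to reach the primary objectives can mean too few centres or incomplete data. This stands, so the futility rule needs narrowing, not removal.
- **A stop need not destroy the study.** That stronger reading is tempting but unsupported. If only recruitment ended, follow-up could continue; if the stop came after 2026, short-term benchmarks would lose no precision.
- **Boundaries and look times may sit in a full protocol or analysis plan.** Agreed, and their absence is not part of this point. The point is that the article adopts a stopping reason that does not fit its design.
- **Exclusive access.** One might argue that it is contradicted because centre data "can be downloaded locally and used for internal quality analyses or institutional research", or because participants are to be told key findings. Neither shows that anyone outside the committee sees pooled interim results. The real tension is inside Interim Analyses, between exclusive access and reporting to stakeholders.

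**Conclusion.** The concern holds for the efficacy stop. The article states a stopping reason with significance thresholds that has no matching primary contrast in a nonrandomized benchmarking registry, and the only contrast that could trigger it is confounded by indication. This is a misfit in what is written, not missing detail.

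The possible loss depends on when a stop came and what it ended. For a full stop under uniform accrual, the follow-up loss runs from total (before 2026) to small (late 2028). The precision loss runs from a factor of about 1.41 at mid-2025 to none from end 2026. These are scenarios, not forecasts: the article fixes no look in mid-2025, its example milestones are follow-up completion or event counts, and an individual centre's factor depends on its own accrual.

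The sample-size and access statements are smaller wording conflicts that belong in the same revision.

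**What to change.** In Interim Analyses:

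- Delete the efficacy stopping reason and the significance thresholds attached to efficacy.
- Restrict futility to operational feasibility, meaning recruitment and data completeness.
- Replace the efficacy looks with scheduled reports on data quality, completeness and descriptive benchmarks.
- State whether any stop ends recruitment only or follow-up as well.
- Leave the safety review in place.
- Reconcile the committee's exclusive access with the promised reporting of interim results to stakeholders, for example by saying which results go to whom and when.

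Reconcile Sample Size with Recruitment, so that either no target is mentioned or the target is given. Do not suspend centres' local use of their own data: the case does not need it, and it would take away something the article offers them.

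The cost is a wording amendment. The study gives up an early-stop option that it could not validly use.

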#### Methods for Additional Analyses

Other studies, including subgroup and adjusted analyses, will explore variations in treatment effects among different patient subgroups. Adjusted analyses will account for potential confounding factors, such as baseline characteristics and comorbidities, that may influence study outcomes. Statistical methods, such as regression models and stratification, will be employed to assess the impact of variables on study outcomes.

Predefined subgroup analyses will be based on key demographic and clinical variables, such as age, tumor stage, and treatment modality. Criteria for conducting subgroup analyses will be established to avoid data-driven post hoc analyses, and exploratory analyses may be performed to generate hypotheses for future research. Sensitivity analyses will assess the robustness of findings by varying assumptions or statistical methods.

Multiplicity issues in subgroup analyses will be addressed by adjusting significance levels and applying appropriate statistical corrections, such as Bonferroni adjustments, to control for type I errors. Guidelines for interpreting additional analyses will be established, distinguishing between confirmatory and exploratory findings. Reporting standards will be adhered to, and results will be presented with effect sizes, CIs, and *P*-values for transparency and reproducibility.

The findings of additional analyses will be reviewed to ensure methodological rigor and validity. Publication policies will be defined, and any deviations from the original study protocol will be disclosed. Additional analysis findings will be communicated to relevant stakeholders, including study sponsors, regulatory authorities, and the scientific community, providing context for interpretation and discussing the implications on the overall study results.

#### Methods in Analysis to Handle Protocol Nonadherence and Any Statistical Methods to Handle Missing Data

The primary analysis will adhere to the intention-to-treat (ITT) principle with consideration of participants based on their randomized treatment assignment. Protocol nonadherence, such as deviations from the assigned treatment, will be captured and addressed in sensitivity analyses, including per-protocol analyses.

Sensitivity analyses will be conducted to assess the impact of protocol nonadherence on study outcomes. These analyses may include per-protocol analyses, where only participants strictly adhering to the protocol are considered, providing insights into the robustness of the primary ITT analysis.

Multiple imputation methods will be employed to handle missing data. Missing data patterns will be carefully examined, and imputation models will be used to estimate missing values based on observed data, enhancing the completeness of the data set. The missing data mechanism will be assessed to inform the selection of appropriate imputation methods with consideration of mechanisms such as missing completely at random (MCAR), missing at random (MAR), or missing not at random (MNAR).

Imputation models that account for variables associated with missing data, including baseline characteristics, treatment assignment, and relevant covariates, will be developed. The number of imputations will be specified to ensure sufficient imputations to capture uncertainty associated with missing data, commonly using 5 or 10 imputations.

Sensitivity analyses will compare results from the imputed data set with those from observed data to assess the impact of imputation on study outcomes. The methods used to handle missing data will be reported in study publications, transparently communicating any assumptions made during imputation and their potential implications on the study findings.

External validation of imputation models will be considered to enhance the generalizability of imputed data. Collaboration with statistical experts will be sought to ensure the appropriateness and rigor of the chosen methods for handling missing data, with input from experts during the planning phase to adapt methods as needed based on recommendations.

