### Trial Design

The Italian Lung Cancer Observational Study (LUCENT) is a prospective observational multicenter cohort study enrolling lung cancer patients who are candidates for minimally invasive manual, robot-assisted, or traditional open surgery. This study aims to investigate the outcomes of patients with early and locally advanced lung cancer in Italy. By using real-world data and patient registries, the study seeks to provide comprehensive insights into the clinical, psychosocial, and economic impacts of lung cancer treatment. The study’s observational nature allows for data collection in a naturalistic setting without intervention or manipulation by the researchers. The list of collaborating institutions has been provided in Multimedia Appendix 1.

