#### Intervention Description

The interventions in this study encompass a spectrum of surgical approaches for lung cancer patients diagnosed in the early and locally advanced stages.

Regarding the rationale for intervention selection, the choice of interventions reflects the diversity of surgical practices in treating lung cancer. Each intervention has its advantages and considerations, and the study aims to evaluate and compare their outcomes comprehensively. Including minimally invasive and robot-assisted surgeries acknowledges the evolving landscape of surgical techniques, aligning with the contemporary emphasis on reducing patient morbidity and improving recovery.

Patients meeting the inclusion criteria will be assessed for eligibility, and the choice of intervention will be based on factors such as tumor characteristics, patient condition, and the surgeon’s expertise.

Qualified and experienced health care professionals will perform the surgical procedures at participating institutions. Data related to the interventions, perioperative details, and postoperative outcomes will be systematically collected through the web-based registry developed for the study.

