### Assignment of Interventions: Allocation

Sequence generation, concealment mechanism, and implementation are not applicable as this is a nonrandomized observational study.

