## Discussion

The protocol outlined in LUCENT presents a robust framework for conducting a comprehensive observational study focused on lung cancer patients in Italy. The study’s emphasis on real-world data collection and patient registries provides a valuable opportunity to gather longitudinal data on various aspects of patient care and outcomes, particularly in the context of minimally invasive surgery for lung cancer. One key strength of the protocol is its adherence to the ITT principle, ensuring that participants are analyzed based on their randomized treatment assignment. By incorporating sensitivity analyses to address protocol nonadherence and employing multiple imputation methods for handling missing data, the study demonstrates a commitment to rigor and transparency in data analysis. Furthermore, the protocol’s plan for auditing trial conduct at regular intervals, independent of investigators and sponsors, underscores the importance of maintaining data integrity, participant safety, and regulatory compliance throughout the study. The comprehensive audit reports and corrective actions in response to findings reflect a proactive approach to quality assurance and risk management. The protocol also highlights the importance of transparent communication regarding protocol amendments, ensuring that relevant parties are informed of any significant changes that may impact the study’s conduct or outcomes. By prioritizing clear and explicit communication with participants, ethical committees, and other stakeholders, the study aims to uphold trust and accountability in its research practices. Regarding data sharing and dissemination, the protocol outlines plans to make the full study protocol, participant-level data set, and statistical code publicly accessible. By leveraging reputable data-sharing platforms and repositories, the study aims to promote research transparency, collaboration, and reproducibility while prioritizing participant confidentiality and ethical data use. Overall, the LUCENT protocol demonstrates a comprehensive and meticulous approach to conducting an observational study in lung cancer research. By incorporating robust methods for data analysis, quality assurance measures, and transparent communication strategies, the study sets a strong foundation for generating valuable insights into the outcomes of lung cancer patients undergoing minimally invasive surgery in Italy.

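### The primary analysis is defined by a randomized assignment that this nonrandomized study does not have, and the planned risk adjustment is not tied to it

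*Protocol article*

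**What the plan says.** The section of the protocol article on protocol nonadherence and missing data sets the rule for the primary analysis: "The primary analysis will adhere to the intention-to-treat (ITT) principle with consideration of participants based on their randomized treatment assignment". Departures from the assigned treatment go to sensitivity analyses, including a per-protocol analysis "where only participants strictly adhering to the protocol are considered". The same section lists treatment assignment among the variables for the imputation models. The Discussion presents the ITT principle as a key strength, "ensuring that participants are analyzed based on their randomized treatment assignment".

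Other sections describe a different study. Allocation says: "Sequence generation, concealment mechanism, and implementation are not applicable as this is a nonrandomized observational study". Trial Design says the observational approach "allows for data collection in a naturalistic setting without intervention or manipulation by the researchers". Intervention Description says "the choice of intervention will be based on factors such as tumor characteristics, patient condition, and the surgeon’s expertise".

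On adjustment, the primary objective (stated under Objectives and again under Outcomes) is to build national benchmarks from risk-adjusted outcomes and care-process indicators, and to compare centres with them. Methods for Additional Analyses plans regression and stratification to deal with confounders. Statistical Methods for Primary and Secondary Outcomes names 1-way ANOVA for differences between groups, and multiple linear regression on participant characteristics. The sections on the choice of comparators and on the interventions say that outcomes of the surgical approaches will be compared.

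**The concern.** An ITT rule needs a recorded assignment that precedes treatment and does not depend on prognosis. Randomization supplies one; clinical choice does not. If the primary rule points to a variable that was never generated, an analyst must replace it with something else: the treating centre, the planned approach or the completed approach. These answer different questions, and the document does not choose between them.

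Two things are at stake. First, the primary objective compares centres with a national standard, and grouping by treatment assignment, randomized or not, does not define that comparison. Second, where approaches are compared, the factors that drive the choice of approach are likely to be prognostic, so a crude contrast carries confounding by indication. Calling the analysis ITT by randomization, and listing that as a strength, invites readers to give the contrast a protection it lacks.

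**Working it through.** The document gives no sample size, effect size, event rate or significance level on this point, so there is no stated figure to reproduce. The check is mainly one of consistency.

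**1. Does the grouping variable exist?** The primary rule groups by randomized assignment. Allocation says "not applicable as this is a nonrandomized observational study" of sequence generation, concealment and implementation. No randomized assignment is produced, so the rule cannot be executed as written.

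**2. Is this an isolated slip?** No. The Discussion repeats the randomization wording and takes credit for it. Condensing a longer protocol does not explain a false statement made twice.

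**3. What else depends on it?** The per-protocol analysis needs an assigned treatment to adhere to. The study assigns none and does not manipulate treatment, so that set is undefined too. The imputation models name the same missing variable.

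**4. Does another section supply the right rule?** In part.
- The primary objective calls for risk-adjusted outcomes, but the primary analysis rule does not mention centres or risk adjustment.
- Methods for Additional Analyses adjusts for baseline characteristics and comorbidities, but as additional work, not as the primary analysis.
- The 1-way ANOVA is unadjusted. Its groups are an open-ended list that does not name surgical approach; treatment modality appears as a subgroup variable under additional analyses.
- The multiple linear regression concerns participant characteristics and is not said to include surgical approach.

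Adjustment is therefore planned but attached to neither the primary rule nor the stated group comparison.

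**5. Illustration of a crude approach contrast.** All inputs are assumptions. One binary severity marker is present in p1 = 0.6 of open cases and p0 = 0.3 of minimally invasive cases, and it multiplies outcome risk by R. Approach has no true effect. The crude open versus minimally invasive risk ratio is

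(1 + p1(R − 1)) / (1 + p0(R − 1))

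- R = 1.5: 1.30 / 1.15 = 1.13
- R = 2: 1.60 / 1.30 = 1.23
- R = 3: 2.20 / 1.60 = 1.38

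With equal prevalences the ratio is 1.00. With the prevalences reversed it is the reciprocal: 1.15 / 1.30 = 0.88, 1.30 / 1.60 = 0.81 and 1.60 / 2.20 = 0.73. Size and direction thus depend wholly on the assumed imbalance.

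**The case against.** The strongest reply is that the protocol is open about its design and does plan adjustment. Allocation states plainly that nothing is randomized, the primary objective rests on risk-adjusted outcomes, and confounders are to be handled by regression and stratification. On that view the word 'randomized' is left over from a trial template, and an analyst would read 'assigned' as 'planned'.

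Much of this stands, and it rules out some stronger readings. A reader might infer that no adjustment is intended, or that approach comparisons will be reported as causal; the document says neither. A reader might also infer that operations converted to open surgery would be moved to the open group, which would flatter the minimally invasive groups. Conversion is not mentioned, and its detailed handling may sit in an analysis plan that is not shown. The risk ratios above show what confounding can do to any crude comparison. They are not an effect of the wording, and the planned adjusted analyses address that problem where they are applied.

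The reply does not remove the contradiction. The sentence that fixes the primary analysis is false for this design and is repeated as a strength, and nothing in the article says which grouping replaces it. Reading 'assigned' as 'planned' would still leave the primary objective, a comparison of centres, without a matching analysis rule.

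**Conclusion.** The point holds as an error in what the document states, not as an omission. The primary analysis groups and the per-protocol set do not exist as written, and the planned risk adjustment is linked neither to the primary rule nor to the ANOVA. Comparisons of surgical approach could be read as protected by randomization when they carry confounding by indication; that they would be reported this way is not established.

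This conclusion rests on the text alone and needs no numerical assumption. The size of any bias cannot be derived from the document. The range 1.13 to 1.38 depends on the assumed prevalences and risk multipliers and is illustrative only. The study can still be analysed by centre or by surgical approach once the rule is stated. The correction should be made before analysis begins, because it concerns the defining rule of the primary analysis.

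**What to change.** - **Nonadherence and missing-data section, and Discussion:** delete 'randomized' and the claim that ITT is a strength. In the imputation models, replace treatment assignment with the grouping variables defined below.
- **Primary objective:** state that the primary analysis is a case-mix-adjusted comparison of each centre with the national benchmark, with patients grouped by treating centre. Do not adjust this analysis for centre or surgeon, because that would remove the between-centre differences it is meant to estimate.
- **Surgical-approach contrasts:** group by the approach planned at the start of the operation. Make the covariate-adjusted estimate the main one in place of the crude ANOVA, using the determinants named in the Intervention Description and accounting for centre. The regression or stratification already planned can serve.
- **Sensitivity analysis:** replace the per-protocol analysis with one grouped by the approach completed.
- **Reporting:** describe approach contrasts as associations.

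The cost is wording changes and a little more analysis, with no extra patients. If the registry does not already record planned and completed approach separately, it needs a field for this. The registry data set is not shown. Recruitment is scheduled to run to the end of 2026, and planned approach is most reliable when recorded prospectively, so any such field is best added early.
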